### ISs

*PracticeGround*, an internet-based EBP training and learning community platform, will be used as the platform for IS meetings in this study. It has capacity for usage metrics and provision of CE credits. Previous research demonstrated its effectiveness as a platform for EBP training [73, 74]. A full range of materials for CPT online support (e.g., webinars, video clips, presentations, and handouts on CPT-related topics) have been integrated into PracticeGround.

Each IS cohort will include a maximum of eight clinicians across up to two clinics within the same system. After a 2-hour web-based learning (for CQI) or booster (for FID) sessions, they will meet biweekly for the first 3 months, then monthly over the last 9 months of the [12-months] active intervention phase, with between-meeting message board correspondence and communication within individual clinics. We will review recordings to assess adherence to the FID or CQI manual and differentiation of ISs with a checklist based on a review of CQI elements and the key IS elements identified in the manuals [75] and will track correspondence within each condition to compare communication.

### Fidelity-oriented consultation (FID)

FID will be led by a CPT expert using structured format based on the effective standard CPT consultation model [4, 5, 76]. One hour meetings will consist of fidelity (adherence and competence) feedback based on discussion of cases and session audio review during the meeting, with guidance on challenges to CPT fidelity, e.g., how to use CPT without deviation from the manual. Participants will also review CPT training modules to improve fidelity. Facilitators will be certified CPT consultants. PDSA cycles will not be used.

### CQI learning collaborative (CQI)

CQI facilitators have been trained in CQI and LC strategies by study team members who have experience in facilitating CQI-oriented LCs. The framework for the CQIs is based on the Institute for Healthcare Improvement’s Breakthrough Series collaborative model for quality improvement [77], which has been used successfully in mental health [61]. Prior research indicated that in-person learning sessions do not add a significant value relative to associated costs [78], so initial learning sessions will be trainings in CQI principles that will occur on PracticeGround. Action periods take place between subsequent hour-long Web-based meetings, allowing time for each team to implement change ideas identified during meetings and study the effectiveness of those change ideas using the Plan-Do-Study-Act (PDSA) cycle of learning. Examples of goals might include increasing CPT engagement, improving effectiveness for individuals with particular symptom profiles, or advocating for more frequent sessions within the clinic. Consistent with the CQI model, non-clinicians who are the key to producing change can participate in the CQI meetings to facilitate change.

### Hypotheses and assessment strategy

We propose to assess the impact of CQI and FID on a variety of the key implementation outcomes with the following hypotheses:Patient symptom improvementOur primary outcome, change in PCL-5 scores, non-inferior for CQI as compared to FIDOutcomes for ISs will be superior to outcomes for patients seen during the no intervention phaseThe ISs will impact change in symptoms through different mechanisms (increased fidelity for FID [30, 79], CPT adaptation, and development of learning organizations for CQI) [64]
Cost, as measured by budget impact, will be greater for CQI, which requires increased personnel burden (management involvement and activities between meetings) [61], than FID.Fidelity (adherence and competence) will be greater for FID, which targets fidelity [54], than CQI [60].Adaptation (# of changes to CPT) will be greater for CQI than FID due to planned adaptations in CQI [60].Penetration (% of eligible patients who receive CPT) will be greater for CQI than FID, as CQI targets barriers to patient enrollment and retention and allows adaptations to improve fit [60].Workforce capacity (% of clinicians who receive CPT provider status) will be greater for FID, which is intended to improve skills and promote adherence [54], the benchmarks for quality-rated provider status.Organizational capacity (learning organization status and implementation climate) will be greater after CQI, which facilitates development of learning organizations [64] and reduces barriers to implementation [60, 80].

### Patient measures

To examine hypotheses 1A and B, we will use the posttraumatic stress disorder checklist (PCL-5), a validated 20-item self-report measure that assesses the 20 DSM-5 symptoms of PTSD [71] that patients routinely complete in CPT. Each item is measured on a 5-point Likert scale. These are recorded in VA clinical records and can be extracted at the clinic and patient level. VAC collects the PCL-5 in their secure, Web-based Client-Reported Outcome Monitoring Information System (CROMIS), which is based on the OQ outcomes monitoring system [81]. For CPT patients, PCLs are done at pre-treatment, at every CPT session, at post-treatment and 3-months post-treatment, for a total of 12–15 administrations.

### Additional patient measures

Patient demographics and diagnoses will be collected from clinicians and used as covariates in analyses. Patients will also complete The Outcome Questionnaire-45 (OQ-45), a validated, 15 min measure of functioning and other key outcomes of interest (symptoms, interpersonal problems, social role functioning, and quality of life) that are of interest in mental health [82, 83] (baseline, mid- and post-treatment) and the Patient Health Questionnaire (PHQ-9) [84] to assess symptoms of depression (at every session). They will complete a post-treatment Client Satisfaction Questionnaire (CSQ-8) [85] to assess satisfaction with treatment at the end of treatment.

### Cost (budget impact)

To test hypothesis 2 and lay the groundwork for future, more comprehensive economic evaluations, we will use a framework for best practices for budget impact analysis [86].

### Clinician CPT fidelity assessment

#### Observer-rated fidelity measures

We will assess fidelity for hypothesis 3 and as a potential mechanism of change (hypothesis 1C) via observer ratings of a randomly selected subset of session recordings. The CPT fidelity measure (Nishith and Resick Cognitive Processing Therapy Fidelity Scale. Unpublished Manuscript) examines clinicians’ adherence and competence to specific CPT interventions prescribed in each session. Clinicians are rated on their adherence to the protocol (i.e., the degree to which they performed a particular task, on a 0–2 Likert-type scale) and competence in delivery of these elements (rated on a 7-point, Likert-type scale). Sessions will be continuously uploaded by clinicians to a secure server (using procedures that were successfully used with geographically dispersed clinicians in our consultation study) [62, 87] and randomly selected for rating to minimize bias that may occur if clinicians were instructed to only provide sessions at designated time points. Rater agreement will be maintained through ongoing training, and raters will rate at least 15% of the sessions to assess reliability.

#### Self-reported adherence measure (secondary measure of fidelity)

As a routine aspect of documentation, at every session, clinicians will complete a 5–8-item adherence checklist for “unique and essential” CPT elements that are embedded in required VA template clinical notes and which will also be embedded in the CROMIS/OQ platforms.

### Adaptation

To assess adaptation (hypothesis 4), we will use a framework and coding system of modifications and adaptations made to EBPs [88] that has previously been applied to interview and observation data on CPT adaptation [26]. Session recordings will be independently rated to identify modifications.

### Penetration, clinician satisfaction, LC engagement, and CPT activity reporting (P&S)

As in our consultation study, at baseline, 4, 8, and 12 months, and at the follow-up, clinicians will complete a survey on CPT activity. Questions will include number/proportion of PTSD cases who received CPT since the last assessment, number of CPT sessions delivered, satisfaction with the IS over the past month; frequency of non-study consultation or training; contextual adaptations; and confidence in CPT delivery. To assess the validity of self-reported penetration, detailed interviews with a subset of clinicians will assess eligibility of each patient with PTSD on the caseload and identify CPT elements utilized with each.

### Capacity

To measure workforce capacity to deliver CPT (hypothesis 6), we will examine the proportion of clinicians in each clinic who qualify for a more advanced form of provider status, quality-rated CPT provider status (QRCPS) at each assessment. QRCPS is awarded to clinicians who have conducted CPT with at least three patients in the past year, and who achieve an average of two (out of three points) or higher adherence score and an average of four (out of six, indicating good) competence scores on a randomly selected session.

To assess organizational capacity and contextual factors (hypothesis 7), we will use two measures.

The Learning Organization Inventory (LOI) [80] is a psychometrically valid assessment of learning environment, concrete learning processes, and whether leaders reinforce learning. Given the potential for CQI to foster development of learning organizations, LOI will be assessed at two additional times for our analysis of potential mechanisms. We will also assess organization- and clinician-level constructs that have been associated with implementation success in prior research [27, 89]. The Implementation Climate Assessment (ICA) [89] will be used as an additional measure of capacity.

### Potential moderators (exploratory)

Additional measures will be used to explore organization- and clinician-level moderating effects on the impact of ISs and/or use of EBPs, they will be administered at the baseline, 4-, 6-,12-, and 24-months timepoints (also to examine change over time) of the study [90].

The Organizational Social Context (OSC) measures climate, culture, and work attitudes. It is psychometrically sound [91] and predicted sustainability in prior research [27].

The Implementation Leadership Scale (ILS) [92] is a brief measure of (1) proactive, (2) knowledgeable, (3) supportive, (4) perseverant leadership with excellent internal consistency, convergent, and discriminant validity.

The Clinician Demographic Characteristics and Experience Questionnaire (CDCEQ) will be administered at baseline to assess relevant clinician demographic information and experience.

The Perceived Characteristics of Intervention Scale (PCIS) [93] is a brief survey that assesses innovation characteristics first identified by Rogers that are hypothesized to influence adoption and sustainability [93].

### Interviews and qualitative strategy

We will also interview a subset of clinicians and administrators to contextualize and extend findings from the quantitative data collection. We will sample from each clinic at baseline. At post-LC and follow-up, a purposive sampling strategy will be utilized to ensure representation across systems and to capture perspectives of clinicians and administrators who experience different outcomes within each IS condition (e.g., low vs. high penetration, fidelity, and CPT utilization). The interviews will assess multilevel influences on engagement in ISs and on CPT delivery. The interview guide will be based on the tenants of the DSF [60] and the Consolidated Framework for Implementation Research [94].

#### Analytic strategy

We will examine descriptive statistics and distribution of all variables. Outcome variables will be transformed as needed if data violate assumptions of normality. We will evaluate effectiveness of randomization by comparing baseline measures of the key variables and demographics using χ^2^ and *t* tests.

##### Aim 1

The first aim is to examine the impact of two LC interventions for sustained EBP delivery on the use and effectiveness of CPT. We will test hypothesis 1A (non-inferiority of FID relative to CQI) by examining [95] whether the difference in change between the groups after the ISs is complete (12 months) and at follow-up is smaller than a predetermined clinically reliable difference (i.e., the non-inferiority margin “delta”).

To estimate change, we will use multilevel regression (i.e., growth curve analyses, mixed effect regression, hierarchical linear modeling), which offers numerous strengths for analyzing change over time for nested data, including efficiency in handling missing data, powerful and accurate estimation procedures adjusting for clustering, and modeling flexibility (e.g., allows for the inclusion of continuous or categorical, time invariant or time varying, covariates and predictors). This approach is extremely robust to missing data and considered “state of the art” for analyzing unbalanced data sets due to dropouts and loss to follow-up [96].

A three-level model will be evaluated to test the impact of IS on change in PTSD. Time (since pre-treatment) will be entered as a level-1 predictor to estimate change in PCL-5 scores. Level 2 will be included to account for the individual assessments nested within patients. Since randomization occurred at the clinic level, IS (dummy coded variable) will be entered as a level-3 predictor to examine the impact of IS on change over time in PTSD symptoms. Given the small number of systems, system will be a level-3 (clinic level) variable to assess and adjust for its influence. We will examine the influence of potentially significant covariates (e.g., baseline PCL-5, VA vs. community; veteran status, other clinician, or patient characteristics/diagnoses) and include in analyses if necessary.

To examine hypothesis 1B (that both ISs will be superior to no intervention), we will conduct piecewise multilevel growth modeling, which will allow us to estimate separate trajectories for each phase of the study by condition. This approach is being increasingly used in randomized controlled trials to more clearly elucidate change across multiple phases [97].

To further compare the impact of the ISs to no intervention (hypothesis 1B), we will use PCL and diagnostic data extracted from VAC’s CROMIS and the VA records. We will separately examine administrative PCL data for all patients with PTSD seen by VAC and VA clinicians through CROMIS and VA’s clinical CPT templates and clinical reminder data, both of which have capacity for clinic and clinician-level linkage and data extraction.

Hypothesis 1C. Different mechanisms of change will be evident for the two ISs. We hypothesize that FID will impact outcomes through increased fidelity and that CQI will impact outcomes through adaptation and development of learning organizations. Lagged regression modeling is a useful way to examine temporal precedence between contemporaneous time-varying phenomena, where a causal effect of variable X1 on X2 is established when X1 at time 1 significantly contributes to the behavior of X2 at time 2 while controlling for the effect of X2 at time 1 [98, 99]. To evaluate temporal precedence, lagged multivariate multilevel models will be evaluated [100]. Multivariate models will allow for the inclusion of two outcomes in the same model [100]. Each of the outcomes will be predicted by the level of that outcome at the previous time point (i.e., autoregressive effect, e.g., PTSD at time 2 will be predicted by PTSD at time 1) and the other variable (observer-rated fidelity, adaptation, or LOS score) in the model at the previous assessment occasion (i.e., cross-lagged path PTSD will be predicted by the proposed mechanism and vice-versa). We will also account for overall increases and decreases in the model by including time as a predictor of each outcome.

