### Summary of the proposed project

Clinics in three mental health systems that have implemented CPT for PTSD will submit baseline session recordings and patient data for at least two patients (*n* = 192) before random assignment to either 12 months of FID (*n* = 16 clinics, 48 clinicians, 192 patients), or CQI (*n* = 16 clinics, 48 clinicians, 192 patients). Outcomes will include patient self-reported PTSD symptom outcomes (primary); independent fidelity ratings; and penetration, adaptation, and capacity to deliver CPT [46, 69]. We will also investigate engagement in, credibility and costs of, and satisfaction with each IS [mechanisms by which the interventions impact patient outcomes] as well as contextual factors that may impact sustainability. The mixed method design will include qualitative methods for a richer understanding of the process and outcomes for each of the ISs [70]. This study will capitalize on infrastructure created for a previous trial comparing EBP consultation strategies [59] as well as existing infrastructure in the participating mental health systems and strong collaborative relationships and experience with each participating mental health system. The study has the potential to advance implementation science beyond observational studies of EBP sustainability by providing much-needed information on the effectiveness of interventions to promote long-term EBP implementation.

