### Randomization and timeline

Randomization will occur at the clinic level. Given the relatively small number of clinics, a stratified randomization procedure will be used to match the ISs (after baseline) on size (# of clinicians in each clinic) and system. The statistician will create a block for each combination of covariates and assign each clinic to the appropriate block. Simple randomization will occur for clinics within each block. As illustrated in the timeline, ISs will occur in three waves, and within each wave, clinics will be randomized further into immediate or delayed (6 months) start. This will facilitate a comparison with no IS [72] using symptom and session data collected from the baseline phase of the delayed start group. Administrative data from before and during the IS phase will facilitate further comparison of symptom change for patients seen before vs. during ISs. During baseline and to keep the delayed start group engaged, we will offer webinars to introduce study technology and provide general updates on CPT research findings (with no guidance for actual practice). Incentives for engagement in baseline include written fidelity feedback from one baseline session after the IS phase starts, clinician and clinic-level gifts for providing baseline data, and CE credits for webinars.

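### The primary 1A model leaves all covariates except system to judgement, does not name the clinic-size stratum and makes no use of the pre-randomization patients; separately, the baseline tests ignore clinic-level allocation

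*Protocol article*

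**What the plan says.** **Model terms.** Under Analytic strategy, Aim 1, the three-level growth model has time since pre-treatment, the implementation strategy (IS) as a clinic-level term, and system: "system will be a level-3 (clinic level) variable to assess and adjust for its influence". On further covariates it says "We will examine the influence of potentially significant covariates (e.g., baseline PCL-5", adds examples, and ends "other clinician, or patient characteristics/diagnoses) and include in analyses if necessary". It gives no criterion for necessity. The section Additional patient measures, by contrast, makes patient demographics and diagnoses covariates without any condition.

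**Allocation.** Under Randomization and timeline, "a stratified randomization procedure will be used to match the ISs (after baseline) on size (# of clinicians in each clinic) and system". The same paragraph adds "Simple randomization will occur for clinics within each block".

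**Baseline checks.** The opening paragraph of Analytic strategy states "We will evaluate effectiveness of randomization by comparing baseline measures of the key variables and demographics using" chi-square and t tests. It names no allowance for clustering.

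**Baseline-phase patients.** According to the Summary of the proposed project, clinics will "submit baseline session recordings and patient data for at least two patients" before random assignment (192 in all). The sample-size section counts them as two per clinician. The stated analytic use of their symptom scores is the comparison with no intervention (hypothesis 1B).

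**The concern.** The 1A result rests on 32 clinics and also informs the choice between the two strategies on cost. Three features of the model weaken it.

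- An open covariate list with no entry rule lets the non-inferiority conclusion depend on which model is fitted. The two sections that mention demographics and diagnoses cannot both govern that model.
- One stratification factor is carried into the model and the other is not named. Simple randomization within blocks does not guarantee balance within a block, which adds to the reason to adjust for size.
- Baseline PCL-5 has no settled role. With time counted from pre-treatment, and baseline listed among the nine outcome time points in the sample-size section, the score is already the time-zero outcome. Entering it as a covariate as well would use it twice.

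There is also an opportunity not taken. Each clinic supplies patients treated before randomization, whose outcomes carry information on the clinic effect, and 1A does not draw on them.

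The baseline tests are a separate problem. Tests that treat patients as independent under clinic allocation will report chance imbalance too often.

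**Working it through.** **Inputs.** From the sample-size section: clinic ICC 0.12, SD 7, 32 clinics, three clinicians per clinic, four IS-phase patients per clinician (12 per clinic, 16 × 12 = 192 per arm), and two baseline-phase patients per clinician (6 per clinic, 32 × 6 = 192). Assumptions: ICC 0.05 as a lower value; the clinic ICC for PCL scores also holds for PCL change and for other baseline variables; and a cluster autocorrelation (CAC, the correlation of a clinic's effect between phases) of 0.6 to 1.0.

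**The protocol's design effect.** DE = 1 + (m − 1) × ICC = 1 + 11 × 0.12 = 2.32, which reproduces the stated figure.

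**False flags from unclustered tests.** True error of a nominal 5% patient-level test = 2 × (1 − Φ(1.96/√DE)).

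| ICC | Patients per clinic | DE | True error |
|---|---|---|---|
| 0.12 | 6 | 1.60 | 0.121 |
| 0.12 | 12 | 2.32 | 0.198 |
| 0.05 | 6 | 1.25 | 0.080 |
| 0.05 | 12 | 1.55 | 0.115 |

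Simulated patient-level t tests with 6 patients per clinic at ICC 0.12 gave 11% to 13% per variable. With five independent variables, the chance of at least one false flag is 1 − (1 − 0.121)^5, about 48%.

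**Gain from the clinic's baseline-phase mean.** The reliability of a clinic mean is R = m × ICC / (1 + (m − 1) × ICC), and the variance reduction is R₀ × R₁ × CAC².

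- ICC 0.12: R₀ = 0.72/1.60 = 0.45 and R₁ = 1.44/2.32 = 0.621, product 0.279. The reduction is 10%, 18% and 28% for CAC 0.6, 0.8 and 1.0.
- ICC 0.05: R₀ = 0.30/1.25 = 0.24 and R₁ = 0.60/1.55 = 0.387, product 0.093. The reduction is 3%, 6% and 9%.

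On the PCL scale at ICC 0.12, the 95% half-width is 1.96 × 7 × √(2 × DE/192). That is 2.13 points unadjusted (DE 2.32), 1.93 at CAC 0.8 (DE 1.91) and 1.81 at CAC 1.0 (DE 1.67), against the 5-point margin.

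**Joint modelling with an ordinary arm-by-phase term.** In units of total variance, the clinic-mean variances are 0.12 + 0.88/12 = 0.193 (IS phase) and 0.12 + 0.88/6 = 0.267 (baseline phase). A free arm-by-phase contrast is a difference in differences with variance 0.193 + 0.267 − 2 × CAC × 0.12 = 0.220, 0.268 and 0.316 for CAC 1.0, 0.8 and 0.6. Against 0.193 unadjusted, that is a rise of 14%, 39% and 63%.

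**Effect on type I error.** A clinic-level simulation used 32 clinics, ICC 0.12, one or five baseline covariates explaining 0% or 80% of between-clinic variance, and 4,000 to 6,000 runs per setting. Two-sided error at nominal 0.05 was:

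- 0.050–0.055 unadjusted
- 0.052–0.054 with fixed adjustment
- 0.044–0.050 when covariates were chosen by the baseline test
- 0.058–0.083 when the most favourable of the three models was reported

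**The case against.** **A reader might infer that the baseline tests decide which covariates enter.** The text does not say so. Their only stated purpose is to check the randomization, and they stand in a general paragraph ahead of Aim 1. The 12–20% figure therefore concerns the balance check, not the non-inferiority result. It also borrows a PCL-based ICC for other variables.

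**A reader might infer that no adjustment is fixed, or that size is excluded.** System is always in the model. The covariate list is open, and the analysis plan, which is not shown, could name size. This limits the wording to not named. It does not remove the point, because the article states a discretionary rule for the primary model and contradicts it elsewhere.

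**The baseline-phase patients have a purpose.** They are different people from the IS-phase patients and are assigned to 1B, where the piecewise model already separates phases by condition. Leaving them out of 1A is forgone efficiency, not an error. With six patients per clinic the mean is only moderately reliable (0.45 at ICC 0.12), and at ICC 0.05 the gain is slight. This stands, so that term is a preference and not a requirement.

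**The harm to error rates is small.** This also stands: a mechanical pretest rule did not inflate type I error in the simulation.

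**Conclusion.** The point holds in limited form. The 1A covariate set is left to judgement without a criterion and conflicts with the section on additional patient measures. Clinic size is not named although it stratifies the randomization, and baseline PCL-5 has no single defined role. The pre-randomization patients could add precision to 1A but are used only for 1B.

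The cost is analyst discretion and lost precision. Large type I inflation is not shown: even picking the best of three models gave at most 0.083. The precision figures rest on the assumed cluster autocorrelation and on carrying the PCL-level ICC over to change scores.

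The clustering fault in the baseline tests is a distinct and lesser matter. It assumes that they are run as ordinary patient-level tests, as the wording suggests.

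**What to change.** - Pre-specify the 1A covariates: system, clinic-size stratum, and patient pre-treatment PCL-5 in one role, either as the time-zero outcome or as a covariate with time zero removed from the outcome vector.
- Preferably add the clinic's baseline-phase mean PCL-5 change. If baseline-phase patients are modelled jointly instead, constrain the arms to be equal in that phase; a free arm-by-phase term would lose precision.
- Reconcile Additional patient measures with Analytic strategy on whether demographics and diagnoses are always adjusted for.
- Describe baseline balance without significance tests.
- Label any other adjustment as a sensitivity analysis.

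This changes analysis wording only, because all the data are already planned. The price is a few clinic-level degrees of freedom out of 32 clinics. In the simulation, one uninformative clinic-level covariate raised the standard error from 1.078 to 1.095, about 1.6%.
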